## Abstract

**Background:**

Spatial neglect is a common attentional condition post-stroke linked to poor rehabilitation outcomes. Prism adaptation, though a promising intervention, is not yet widely used clinically due to various barriers to its implementation, including limited accessibility, the repetitive nature of the therapy, and the need for specialized equipment. This protocol aims to examine the effectiveness, feasibility, and acceptability of an engaging, mobile, computerized prism adaptation procedure (Peg-the-Mole) for treating spatial neglect in stroke inpatient and outpatient community settings.

**Methods/design:**

The present study uses a longitudinal, double-blind, quasi-randomized, controlled design. Forty-two individuals with right-hemisphere stroke experiencing mild to severe symptoms of neglect will be randomized into two groups: Use of Peg-the-Mole with 15-degree rightward-deviating prism goggles (intervention) or use of Peg-the-Mole with 5-degree rightward-deviating prism goggles (active control). Participants will complete 10 treatment sessions over 2 weeks, engaging with the Peg-the-Mole procedure for 15 minutes daily. Blinded assessments will take place immediately before and after treatment, as well as at one-month follow-up. The primary outcome measure will be the Star Cancellation conventional subtest of the Behavioural Inattention Test. Secondary outcomes will include additional conventional and behavioural subtests of the Behavioural Inattention Test, one subtest of the Eschenbeck Standardized Activities of Daily Living battery, the caregiver- and self-reported forms of the Halifax Neglect Impact Scale, data measuring feasibility and acceptability, prism adaptation after-effects, the Hospital Anxiety and Depression Scale, and the Fatigue Severity Scale.

**Discussion:**

The Peg-the-Mole procedure has the potential to improve patient recovery and quality of life after stroke due to its gamified, portable features that promote treatment accessibility and adherence. Results from this study will help determine if the treatment can be implemented successfully in inpatient and community settings to improve neglect symptoms and daily living.

**Trial registration:**

Clinicaltrials.gov, Identifier: NCT05595668; registered October 27, 2022.

## Introduction

Spatial neglect is a common and debilitating attentional disorder characterized by an inability to detect, orient to, or respond to stimuli presented on the contralesional side of space [1]. This condition is not due to primary sensory or motor impairments [2,3]. It affects approximately 30-50% of stroke patients, often leading to impaired daily functioning, loss of independence, and slower recovery [4–6]. Symptoms of neglect can lead to serious functional impairment and interfere with mobility, navigation ability, reading, and self-care activities such as eating, dressing, and grooming [4]. It is estimated that approximately 40% of individuals with neglect may go on to develop chronic symptoms [7,8]. Given the debilitating impact of spatial neglect on functional independence, individuals often require increased assistance with activities of daily living (ADLs) which in turn may lead to greater caregiver reliance and burnout [6,9]. Loss of independence in everyday life can also reduce quality of life and may contribute to depression, anxiety, and fatigue [10,11]. Moreover, spatial neglect is associated with longer hospital stays and higher re-admission rates, placing additional strain on healthcare systems [12–14]. Taken together, these challenges highlight the need for easily accessible, effective, and standardized rehabilitation interventions that can enhance functional independence, reduce caregiver burden, and alleviate pressure on the healthcare system.

Various approaches are available for the treatment of spatial neglect, but there is currently no universally accepted standard of care [15–17]. Many existing interventions are resource-intensive, requiring clinician supervision and specialized equipment, and they often lack standardized guidelines [17–19]. Further complicating treatment, up to 64% of individuals with neglect experience a comorbid syndrome called anosognosia, a lack of awareness of their deficits [20]. The presence of both spatial neglect and anosognosia can significantly reduce treatment adherence, often leading to poorer rehabilitation and clinical outcomes [20,21]. Treatment methods are generally divided into two categories, bottom-up (i.e., stimulus-driven) and top-down (i.e., goal-driven) approaches. Given the high prevalence of anosognosia in individuals with spatial neglect, a bottom-up approach is often more appropriate, as these individuals may lack the motivation to develop strategies to address a deficit they do not recognize [20]. Prism adaptation (PA) is a promising bottom-up treatment for spatial neglect. This technique involves wearing prism goggles that shift the visual field rightward, with participants repeatedly pointing towards visual targets. Initially, the visual shift causes rightward pointing errors (i.e., direct effects), but with continued reaching, participants adapt until they can accurately point to the targets again. After 10–15 minutes of prism exposure and reaching, removing the prism goggles results in therapeutic effects called after-effects (i.e., a leftward shift in pointing movements), which may reduce the severity of neglect symptoms and improve daily functioning [22–25]. Thus, PA may have high feasibility as a treatment approach, as it requires little training and does not rely on patient strategy or knowledge of their symptoms [18,26].

Two processes are proposed to underlie the development of after-effects induced by PA as described by Redding and Wallace: strategic recalibration and spatial realignment [27–30]. Strategic recalibration is hypothesized to be an immediate response to pointing errors during PA due to the visual shift, with conscious corrections made to reduce errors in subsequent trials. Conversely, spatial realignment is conceptualized primarily as a slow occurring, unconscious process consisting of the remapping of proprioceptive and visual spatial maps to minimize the discrepancy between the position of the hand and the visual location of the target, leading to the development of after-effects. Strategic recalibration may interfere to some extent with the development of after-effects, although it is thought to still contribute to adaptation during PA [27]. Thus, strategic recalibration during PA is typically minimized using equipment such as an occlusion board to block the patient’s view of their pointing movements to prevent immediate self-correction.

The strength of the prismatic shift is an important factor to consider when evaluating the effectiveness of PA treatment. Randomized controlled trials using sham (i.e., clear) goggles as controls, as well as prisms with smaller shifts (5–6 degrees), found no significant therapeutic effects on conventional and functional outcomes [31,32]. In contrast, studies using prisms inducing a shift of at least 10 degrees have shown promising results, with improvements in both symptom severity and functional outcomes [22,25]. Therefore, a shift of at least 10 degrees is generally recommended to achieve therapeutic effects [17,32].

PA has several advantages as a neglect treatment. It is a bottom-up method requiring minimal strategic processing, making it suitable for individuals with anosognosia, as it does not rely on their awareness of symptoms. PA also has a short administration time, typically requiring 10–15 minutes per day for about ten days [33]. Previous research has demonstrated that PA is effective in reducing symptoms of neglect, with some improvements extending to ADLs [22–24,34]. However, PA has certain limitations that need to be addressed. For example, the repetitive nature of typical PA protocols can reduce patient engagement, and the use of specialized equipment such as an occlusion board, used to block the participant’s view of their hand, is required [35,36]. Clinical supervision in a hospital or research setting is required to ensure the correct procedure is followed, resulting in frequent and repeated travel for each treatment session [36]. Previous research also has found inconsistent evidence for the efficacy of PA, likely reflecting the absence of a standardized protocol and uncertainty surrounding which patients are most responsive to the intervention [17]. Chen et al. (2025) highlight the substantial methodological heterogeneity across PA studies, including variation in prism strength, treatment intensity, arm visibility during adaptation, outcome measurement, and patient characteristics (e.g., time post-stroke). Furthermore, not all individuals with neglect benefit from PA, and factors such as neglect subtypes (e.g., perceptual vs. premotor neglect) and time since stroke onset may impact its effectiveness [26,37]. Thus, clinical recommendations of PA remain tentative due to methodological limitations of previous research and inconsistent outcomes [17,38]. Therefore, although PA may be a feasible treatment for spatial neglect at present, its implementation has been limited to date. The current gaps interfering with the clinical implementation of PA underscore the need for standardized, evidence-based protocols that increase accessibility and engagement, thereby improving long-term functional outcomes in individuals with spatial neglect.

To address these barriers to the clinical application of PA procedures, a home-friendly, game-like PA software called Peg-the-Mole (PTM) was developed. In this protocol, participants wear prism goggles and are prompted to touch as quickly as possible a target bull’s eye held by a cartoon mole presented on an iPad. In comparison to typical PA procedures, PTM requires minimal supervision because the software provides automated instructions, feedback, and data recording, allowing participants to complete sessions independently once trained. The program’s game-like interface enhances engagement and motivation. Importantly, PTM incorporates an adaptive algorithm that adjusts target presentation time based on individual performance, encouraging rapid, ballistic movements and minimizing conscious self-correction during pointing. This algorithm promotes the spatial realignment processes underlying PA while reducing the need for specialized equipment (e.g., occlusion boards). Taken together, these features increase accessibility by enabling standardized, engaging delivery of PA in various settings [36].

Initial testing of PTM was conducted in a sample of healthy young adults comparing it to a typical PA procedure using 15-degree rightward-deviating goggles [36]. Results indicated that prism exposure during PTM yielded adaptation and significant after-effects of equivalent magnitude to those observed with a typical PA procedure. Importantly, participants found PTM to be more enjoyable and engaging than the typical PA procedure. Further PTM studies with both healthy young and older adult samples demonstrated that 15-degree prism goggles induced significantly larger after-effects than 5-degree goggles [39]. Additionally, after-effects induced by PTM have generalized to aspects of wheelchair maneuvering (e.g., a significant reduction in the number of right-sided hits), providing evidence that PTM has the potential to generalize to more functional tasks [40]. More recently, a pilot study examined the feasibility of implementing a desktop version of PTM with stroke patients in an inpatient rehabilitation unit. PTM was administered daily for 10 sessions over two weeks by occupational therapists and the protocol was generally found to be feasible and engaging [41]. In the present study, we adapted PTM for iPad administration to enhance flexibility and accessibility for at-home use.

To support the future clinical implementation of PTM, the primary objective of the present study is to examine PTM’s effectiveness in reducing neglect symptoms as measured by the Star Cancellation task of the Behavioural Inattention Test (BIT) [42]. Short-and longer-term effectiveness will be examined in terms of symptom reduction (i.e., does the PTM PA protocol improve neglect symptoms over time?). We hypothesize that participants who complete 10 sessions of PTM PA treatment using 15-degree rightward-deviating goggles will show a greater reduction in the severity of neglect symptoms immediately after training and at one-month follow up, compared to participants using the PTM protocol with 5-degree deviating goggles.

Secondary objectives include (1) examining treatment effects across additional neglect measures, as well as measures of ADLs, (2) evaluating feasibility and acceptability, (3) examining the magnitude of PA after-effects and the relationship between these effects and neglect severity, and (4) exploring changes in psychological outcomes. First, we will examine whether the 15-degree PTM condition leads to broader improvements in neglect symptom severity across additional neglect assessments, as well as improvements in ADL functioning over time. Second, we will evaluate the feasibility and acceptability of using the iPad-based PA treatment in both inpatient and community settings. Feasibility will be assessed based on compliance with the treatment protocol and schedule, while acceptability will be evaluated through patient feedback. PA after-effects (mean difference in degrees of visual angle from pre- to post-PTM) will be measured after each treatment session. We will examine whether the 15-degree condition produces larger after-effects compared to the 5-degree condition. Additionally, we will investigate whether the magnitude of PA after-effects predicts neglect severity. The relationships between neglect severity and psychological variables, including anxiety, depression, and fatigue, as well as changes in these psychological outcomes following participation in the PTM protocol will also be explored. Although fatigue, anxiety, and depression are prevalent post-stroke [43,44], their association with spatial neglect remains underexplored, and these secondary analyses will provide insight into the broader impact of PTM and whether improvements in neglect symptoms may be associated with changes in psychological outcomes and fatigue severity.

## Materials and methods

### Study design and setting

The current study uses a longitudinal, quasi-randomized, double-blind, controlled design to compare the effects of using the PTM protocol with 15-degree versus 5-degree prism goggles, each provided in addition to usual care. The study is registered at Clinicaltrials.gov (NCT05595668) and follows the Standard Protocol Items: Recommendations for Interventional Trials (SPIRIT) guidelines [45]. The present study has received ethics approval from the Nova Scotia Health Research Ethics Board (REB File #:1028679; dated March 6^th^, 2023). All participants will provide written informed consent prior to participation.

Participants will be initially screened for inclusion and exclusion criteria before undergoing a baseline assessment (see criteria below). Participants currently experiencing symptoms of spatial neglect, as determined by the baseline assessment, will be randomized, stratified by neglect severity, to one of two groups: experimental condition (PTM with 15-degree rightward-deviating goggles) or active control condition (PTM with 5-degree rightward-deviating goggles). Each participant will be assigned an “Assessor”, responsible for all assessments, and a “Trainer”, responsible for overseeing the PTM protocol training and scheduling. Trainers will observe participants during the first PTM session to ensure proper adherence to the protocol. Participants will then complete 10 daily training sessions over two weeks (5 days per week), with each session lasting approximately 15 minutes. Assessments will be conducted at 3 time points: baseline (T0), within one week after the final treatment session (T1; immediate follow-up), and within 4–6 weeks after the final treatment session (T2; one-month follow-up). After each PTM training session, after-effects will be measured, and the treatment and after-effects data will be stored on the iPad for later download. At T1, participants will independently set up and complete training in front of their Assessor to confirm their ability to follow the protocol as trained. The study will be conducted both in the community and across various hospital sites in Nova Scotia, Canada. Data collection is currently ongoing. This trial is open to recruitment from June 20^th^, 2024, to August 31^st^, 2027. Data collection is anticipated to be complete by September 2027, and results are anticipated by August 2028. See Fig 1 and Fig 2 for the study schedule and timeline, respectively.

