### Blinding

The Trainer assigned to each participant will not be blinded to the treatment condition, as they are responsible for training participants on the protocol and they will handle the goggles (i.e., 5- or 15-degree). To minimize trainer influence, all trainers receive standardized training from the same supervisor and must demonstrate competence before interacting with participants. Trainers follow detailed, manualized protocols to ensure procedural consistency across both trainers and sessions, and training tasks are fully computerized with automated instructions and feedback. These steps substantially reduce the potential for bias. Assessors will remain blinded to the treatment condition, and participants will not be informed of which treatment they are receiving. As previous research has shown that 15-degree goggles induce significantly larger after-effects than 5-degree goggles when using PTM, 5-degree goggles will be used as an “active control” [39]. Using 5-degree deviating goggles as an “active control” rather than the typical sham (i.e., clear) comparator preserves the double-blind design of the present study. Upon completion of the study, both participants and their Assessors will be asked to indicate which treatment condition they believe was assigned.

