#### Active control condition.

The active control condition follows the same procedure as the experimental condition, with one key difference: participants in the control group wear 5-degree rightward-deviating goggles while completing the exposure task (i.e., PTM). Participants complete the exposure task (PTM) while wearing these 5-degree goggles, providing a mild visual shift that serves as an “active control” to maintain double-blind conditions without delivering the therapeutic effect expected from the 15-degree shift.

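### The Assessor, who is meant to stay blinded, watches the participant complete PTM training at T1, which could reveal the arm before T2 and possibly before the T1 outcomes

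*Protocol article*

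**What the plan says.** Study design and setting gives each participant one Trainer and one Assessor, the latter "responsible for all assessments" (T0, T1 and T2). For T1 it adds that "participants will independently set up and complete training in front of their Assessor". The stated purpose is to confirm that the participant can carry out the procedure as taught.

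The Blinding section says that "Assessors will remain blinded to the treatment condition". It treats Trainers as unblinded, "as they are responsible for training participants on the protocol and they will handle the goggles". Its check on blinding is a question, put to participants and Assessors once the study is complete, about which arm they think was assigned.

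Under Active control condition, prism strength is the one difference between the arms: "participants in the control group wear 5-degree rightward-deviating goggles while completing the exposure task". On dose, the Abstract says that "Participants will complete 10 treatment sessions over 2 weeks", and Study design and setting gives the same number.

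**The concern.** The person whose blinding protects the outcome assessment is asked to watch the one activity in which the arms differ. The reason given for calling the Trainer unblinded is contact with the training and the goggles, and at T1 the Assessor is in the room with both.

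Two things are at stake. The first is detection bias. An Assessor who has formed a view of the arm may, without intending to, administer or prompt differently. A count of cancelled stars leaves little room in the scoring itself, but its administration leaves some. The form-filling task and the rating scales are more exposed. The second is what T1 measures. If prisms are worn shortly before Star Cancellation, the T1 score may partly reflect that exposure as well as the two-week course.

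**Working it through.** The plan states no figure on this point, so the check is mainly a reading of sections against each other.

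**1. Could an observer pick up the arm?**
- Source of the cue: the Introduction says "Initially, the visual shift causes rightward pointing errors (i.e., direct effects", which participants correct as they adapt.
- Difference between arms: the Blinding section says that "15-degree goggles induce significantly larger after-effects than 5-degree goggles when using PTM".
- Visibility: under Experimental condition, the software gives visual and auditory feedback on accuracy after each response, which a person in the room can see and hear.
- Safeguards for this visit: the text describes no masking of goggles or screen, no other observer and no order of steps.

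The cues are the article's own, so watching could reveal the arm. How large the visible difference is after 10 sessions of practice is not stated.

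**2. Does the order of steps within T1 remove the problem?** The text does not give an order, and the schedule figures are not shown.
- Session before the T1 outcomes: T1 is assessed by someone who has just watched the exposure, and Star Cancellation could also reflect same-visit prism exposure. T2 is then done by the same Assessor.
- Session after the T1 outcomes: T1 is protected on both counts. T2 is still done by an Assessor who has watched the session.

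No order protects T2 while the Assessor is the observer. The T0-to-T1 and T0-to-T2 changes are the two comparisons of main interest under Statistical analyses, so at least one is exposed in either order.

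**3. Session count.** Ten sessions are planned, and T1 falls within one week after the final one. If the T1 session is additional and includes prism exposure, there are 10 + 1 = 11 exposures, 10% more than planned. The T2 window of 4–6 weeks also runs from the final treatment session, so the article should say whether the T1 session counts as one.

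**4. Illustration of size (the bias values are assumptions, not from the document).** Take 21 per group and covariate R² = 0.40 (both from Sample size), with no true effect and a differential assessment bias of b outcome SDs.
- Residual SD = √(1 − 0.40) = 0.775.
- Noncentrality = (b / 0.775) × √(21/2), with 42 − 3 = 39 degrees of freedom (one covariate).
- Two-sided rejection rate at nominal 5%: b = 0 gives 5.0%, b = 0.1 gives 6.9%, b = 0.2 gives 12.9%, b = 0.3 gives 23.2%.

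This shows how sensitive the test is to a small bias. It is no evidence that such a bias will occur.

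**The case against.** The case on the other side is substantial, and much of it stands.

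- **The blind is not shown to fail.** A reader might infer that the double-blind claim collapses at T1. The documents do not support that. The 5-degree comparator was chosen to preserve blinding, and both arms use the same type of goggles with Fresnel prisms. By T1 the participant has had 10 sessions, and no first-trial error is given for either arm at that stage.
- **The Assessor is not in the Trainer's position.** Trainers are told the allocation and handle the goggles. The Assessor is not told it, the participant sets up alone, and there is only one observation. The risk is smaller than the Trainer's, but it is not absent, and an Assessor who sees several participants can compare them.
- **Optical displacement is not pointing error.** One might argue from distance × tan(angle). At an assumed 40, 50 or 60 cm, 15 degrees shifts the image by 10.7, 13.4 or 16.1 cm and 5 degrees by 3.5, 4.4 or 5.2 cm, beside an iPad 21 cm wide. The distance is assumed, and the figures describe the optics, not what an adapted participant does. They do not establish that an observer would see the difference.
- **An acute effect on T1 is conditional.** It requires the session to come first. Step order may be given in the figures or the study manuals.
- **The session counts do not contradict each other.** The Abstract and Study design and setting both say 10. The T1 demonstration can be read as a separate adherence check applied to both arms. What remains is only that its status is unstated.
- **The outcome is a count, and arm guesses are collected.** Both points limit the concern. The guess comes at study completion, so it may detect a loss of blinding but cannot prevent it.

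None of this removes the core: the observer is the Assessor, and that Assessor still has T2 to do.

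**Conclusion.** The point holds as an avoidable risk to Assessor blinding, not as a demonstrated breach. The T1 arrangement in Study design and setting and the statement in Blinding need to be reconciled.

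The risk to T2 holds whatever the order of steps. The risk to T1, both to its assessment and through same-visit prism exposure, holds only if the session precedes the T1 outcomes. As written, the arrangement applies to every participant who reaches T1, up to the planned 42. The size of any bias cannot be derived from the document.

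The conclusion assumes that completing training at T1 means wearing the assigned goggles, which is the natural reading. It does not assume that all 117 exposure trials are run, which the text does not say.

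**What to change.** - For remaining participants, have the already unblinded Trainer observe the adherence check, for example at the last scheduled session or remotely. State in the protocol that the Assessor is not present while goggles are worn.
- If the check stays within the T1 visit, hold it after all T1 outcomes are completed, with the Trainer observing. Cutting it down to set-up without goggles would not do, because it could not confirm that the participant can follow the procedure.
- Reword Study design and setting and Blinding so that they agree, and state whether the T1 session is additional to the 10 planned.

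The cost is wording in the protocol and manuals and one reassigned Trainer contact per participant, with no extra staff. Data collection is ongoing, so the change cannot protect participants who have already passed T1.
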